#### Economies of scale

Costing analyses of MDA programs often assume an intervention’s cost per treatment is constant, regardless of the number of individuals treated. This is a misleading way to consider the delivery costs of MDA, due to the occurrence of economies/diseconomies of scale [28]. This analysis will explore the effect of economies of scale by presenting the cost per person treated at 3 different coverage levels (60%, 80%, 90%).

#### Sensitivity analysis

Univariate and multivariate sensitivity analysis will be conducted to identify main cost drivers and identify a range of potential program costs. The sensitivity analysis will explore changes to the cost of drugs, treatment delivery, security, and per diems, and assumptions around the useful life of capital items. Costs of personal protective equipment associated with COVID-19 prevention will be removed in the sensitivity analysis. The sensitivity of the discount rate will also be varied from 0–6%.

### Community acceptability

#### Antibiotic coverage

Prior to the MDA interventions, a household census will be conducted in all 30 communities whereby all members of all households will be enumerated and the name, sex, and age of everyone will be recorded via electronic census forms. A household member is defined as any person who has lived for at least one month in the household and eats and sleeps in the household. Global positioning system (GPS) coordinates will be captured for each household. The study community census will be used to establish the population to be targeted for study interventions and will provide the denominator for MDA coverage calculations. New residents migrating into study areas after the census but prior to MDA treatment will be added to the census as they are detected. Further, residents unknown to the study team during the MDA treatment will also be added to the census and subsequently treated, if eligible.

During the MDA, each administered dose will be recorded into the electronic record created during the community census by a trained data collector who travels with the distribution team. This record will be used for both study arms to determine the antibiotic coverage during each of the subsequent treatment rounds, allowing for the calculation of the number of doses each participant received. The definition of coverage for this study is: the number of individuals ages 6 months to 9 years who received the drug in study communities in each treatment round divided by the number of children ages 6 months to 9 years enumerated in the baseline census. A secondary analysis will calculate the antibiotic coverage in each round for the age groups 10 to 15 years and ≥ 15 years. Further analyses on compliance will examine the extent and predictors of missed rounds among the 2 study arms.

The dataset on treatment coverage will be compiled quickly by the study coordinator and will be used to monitor the success of the intervention. If the coverage is lower than expected, < 85% among children ages 6 months to 9 years, the treatment team will be redeployed to conduct a community mop-up to improve treatment coverage.

While MDA treatment coverage will be monitored using the census and treatment records, treatment validation will also be conducted. Validation will be based on the WHO endorsed Supervisor’s Coverage Tool [29]. After each round of treatment (either community-wide or targeted) a random selection of 5 study communities will be chosen for treatment validation. A new team will return to a random sample of 20 households in each selected community to assess self-reported treatment within 1 week of treatment. Self-reported coverage from the modified Supervisor’s Coverage Tool will then be compared to the coverage reported in the treatment register.

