### Interventions

Antibiotic interventions will take place at the community level. The first intervention strategy will consist of an enhanced antibiotic regimen comprised of a community-wide MDA, followed by 2 additional rounds of targeted treatment to children ages 6 months to 9 years. The targeted treatments will be distributed 2 weeks and 4 weeks after the community-wide treatment, resulting in 3 doses to children 6 months to 9 years. The second strategy will consist of a community-wide biannual MDA approximately 6 to 8 months apart, resulting in 2 doses for the targeted community. Timing of the second dose will be based on access to communities and at least 6 months after the first dose.

Azithromycin, also known in the global trachoma program by the brand name Zithromax®, is a macrolide antibiotic and is used in the treatment of active trachoma. Zithromax® is donated to the South Sudan MOH for MDA by Pfizer Inc., through the International Trachoma Initiative (ITI). The recommended dosage for the treatment of trachoma is a single dose of 20 mg/kg of body weight and is implemented using an “age-height” based dosing strategy for the trachoma MDA campaigns. Azithromycin can be administrated in either tablet form or powder for oral suspension (POS). Dosing and administration for this study will be conducted following procedures outlined in the Zithromax® Management Guide [15]. To reduce the risk of choking, all children participating in the study intervention ages 6 months to 9 years will receive azithromycin by POS only. Populations ineligible for azithromycin based on national guidelines, including infants under 6 months of age, pregnant women in their first trimester, individuals with a previous history of severe adverse events (SAEs), and individuals with severe illness at the time of MDA, will be offered treatment with 1% tetracycline eye ointment (TEO), to be applied twice daily to both eyes for a 6-week period [15]. Trained drug distributors will facilitate drug administration for the appropriate treatment dose by assessing everyone that presents. Those receiving antibiotic will be directly observed by the distribution team.

Throughout this study, existing S, F, and E interventions will continue through standard programming. This includes offering surgery to individuals identified as needing TT surgery, and advocacy work with water, sanitation, and hygiene (WASH) focused non-governmental organizations operating in the country.

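### The coverage definition counts every child treated over a baseline census list, while the same section adds later residents to the census; the numerator and denominator need to be one population.

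*Protocol article*

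**What the plan says.** The Antibiotic coverage section of the protocol article states a formula. For the numerator it takes "the number of individuals ages 6 months to 9 years who received the drug in study communities in each treatment round". As to the denominator, this total is then "divided by the number of children ages 6 months to 9 years enumerated in the baseline census". The numerator is not limited to children already on the list, and the same denominator serves every round.

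The same section describes a census that grows. "New residents migrating into study areas after the census but prior to MDA treatment will be added to the census as they are detected". In addition, "residents unknown to the study team during the MDA treatment will also be added to the census and subsequently treated, if eligible". It also says that the study community census "will provide the denominator for MDA coverage calculations", here without the word baseline.

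The coverage figure has a field use as well: "If the coverage is lower than expected, < 85% among children ages 6 months to 9 years", the treatment team goes back to the community.

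Round timing differs by arm (Interventions). The child-only rounds come 2 and 4 weeks after the community-wide treatment. The second biannual round comes about 6 to 8 months after the first: "Timing of the second dose will be based on access to communities and at least 6 months after the first dose".

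The secondary coverage analysis uses the "age groups 10 to 15 years and ≥ 15 years".

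**The concern.** A coverage proportion is interpretable when everyone counted above the line could also be counted below it. Here the numerator is open to any eligible child treated in the community, and the denominator as defined is a list drawn up before treatment. Two analysts could follow the section faithfully and report different figures from the same records, one leaving added children out of the denominator and one putting them in.

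Community acceptability is one of the two primary outcomes (Study design overview), and the abstract says it is assessed through coverage monitoring together with mixed-methods work. A coverage figure that moves with migration can be mistaken for a change in acceptance. The same figure decides whether a mop-up is sent, so an inflated value can leave a real shortfall untreated and a deflated one can send a team without need. The gap between list and round is much longer for the biannual second round, so this risk is not shared equally by the arms.

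**Working it through.** **The plan's own denominator.** Setting, eligibility, and participants gives 649 people per community, 30 communities, and 40% aged 6 months to 9 years. 649 × 30 = 19,470 people; 19,470 × 0.40 = 7,788 children; 649 × 0.40 = 259.6, about 260 per community. All three printed figures reproduce. With 1:1 allocation there are 15 communities per arm, so 15 × 259.6 = 3,894 children per arm.

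**Model.** Let *c* be true coverage among eligible children resident at the round, *i* newcomers and *o* leavers (including deaths), both as shares of the baseline list. Children treated = *c*(1 + *i* − *o*).

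- Literal reading: reported coverage = *c*(1 + *i* − *o*).
- Additions in the denominator, leavers still listed: reported coverage = *c*(1 + *i* − *o*)/(1 + *i*).

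The documents give neither *i* nor *o*. The values below are assumptions, with *c* = 85%.

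| Assumed movement | Literal reading | Additions in denominator |
|---|---|---|
| none | 85.0% | 85.0% |
| 5% newcomers | 89.3% | 85.0% |
| 10% newcomers | 93.5% | 85.0% |
| 5% leavers | 80.8% | 80.8% |
| 10% leavers | 76.5% | 76.5% |
| 10% of each | 85.0% | 77.3% |

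The newcomer rows assume that newcomers are treated at the same 85%. If all of a 10% group were treated, the literal figure would be 0.85 + 0.10 = 95.0%. If newcomers join the denominator only when they are treated, the 10% row becomes 0.935/(1 + 0.085) = 86.2%, because untreated, undetected newcomers are never listed.

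**Mop-up check.** Setting reported coverage at 85% on the literal reading: with 10% net growth, true coverage is 0.85/1.10 = 77.3%; with 10% net loss, it is 0.85/0.90 = 94.4%.

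**Exceeding 100%.** On the literal reading this needs net growth above 1/*c* − 1: 17.6% at *c* = 85% and 11.1% at *c* = 90%.

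**Exposure by arm.** The last child-only round is 28 days after the first treatment. At an assumed net migration of 10% a year, that gives 0.10 × 28/365 = 0.8%, about 30 children per arm. At 6 to 8 months it gives 5.0% to 6.7%, about 195 to 260 children.

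**Ageing.** The age window is 114 months. If ages are spread evenly, 6/114 = 5.3% to 8/114 = 7.0% of the list age in over the biannual interval, against 0.92/114 = 0.8% over 4 weeks. A similar number age out, so the net effect on the count is small. The section does not say at which date age is taken.

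**The case against.** The best defence is that the baseline census simply means the electronic census record as later updated. The sentence calling the census the denominator supports this, and additions would then count on both sides. That reading is available, but it contradicts the formula's own wording and leaves leavers in the denominator.

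A reader might go further than the text allows in three ways. First, one might infer that coverage will exceed 100%. That needs the literal reading plus substantial net growth, and it cannot happen if additions are in the denominator. Second, one might infer that the biannual arm is biased in a known direction. The documents give no migration rate, newcomers and leavers offset each other, and ageing largely cancels; only the longer exposure is established. The article also states no formal test of round coverage between arms. Third, one might treat coverage as the only quantitative measure of acceptability. The plan also has community awareness surveys, and it examines doses per participant and missed rounds from individual records. A child who moved away can still look like a missed round, however, if departure is not recorded.

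The validation visits after each round, to 20 households in each of 5 communities, compare self-report with the register. They are a useful check on the numerator but do not settle the denominator.

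Handling of departures and deaths is partly a detail that an article may leave to the full protocol. That stands, and so the main point is the conflict in the stated formula.

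**Conclusion.** The point holds as an internal conflict in a stated definition. The formula pairs an open numerator with a baseline list, while neighbouring sentences enlarge the census and name it as the denominator. Neither reading gives a clean proportion: one mismatches the two populations, the other contradicts the formula, and the text shown has no rule for leavers under either.

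The size is unknown. Under the assumed movement of 5% to 10% in one direction, the literal figure lies between 76.5% and 93.5% when the truth is 85%. At exactly 85% true coverage, inflation does not alter the mop-up decision, since the trigger is a value below 85%. The decision goes wrong when true coverage is lower and growth lifts the figure to the line, as in the 77.3% example, or when leavers pull an adequate figure below it. The biannual second round has the longest exposure.

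Because the ratio feeds a primary outcome and a field decision, it should be settled before the rounds are analysed. The overlapping age bands, in which 15-year-olds fall in both groups, are a minor slip confined to a secondary analysis.

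**What to change.** Reconcile the two denominator sentences and define coverage on matched populations:

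1. **Baseline-census cohort.** Children listed at baseline form the denominator, the numerator is restricted to those same children by ID, and age is fixed at a stated date.
2. **Updated-census version, reported alongside.** Added residents enter both numerator and denominator.
3. Report the number of children added in each round and arm, and state which version the mop-up check reads.
4. Where a departure or death is learned during a round, record it for all listed children whether or not they were treated, and show coverage with and without their removal. Recording it mainly for untreated children would push coverage upward.
5. Make the secondary age bands non-overlapping: 10 to 14 and 15 years and over.

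Items 1, 2, 3 and 5 cost wording and analysis code; the unique IDs that link census and treatment records already exist (Data collection and management). Item 4 adds one status field and a little field time per round, and it is hard to recover afterwards.

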#### Community awareness and acceptability

A mixed methods approach, including focus group discussions (FGD) and community awareness surveys, will be used to elucidate insights from several groups of key community members on the acceptability and feasibility of enhanced MDA strategies and of targeting children for interventions (Fig. 3).

**Fig. 3 Fig3:**
[figure not shown]
Timing of mixed methods study collection as part of the ETAS study. DD = Drug Distributor; FGD = Focus Group Discussion; MDA = Mass Drug Administration

Three thematic areas will be the focus of the FGDs: 1) Pre-MDA FGDs with drug distributors and MDA field supervisors; 2) Post-MDA FGDs with participating drug distributors; and 3) Post-MDA FGDs with participating community members. The community awareness surveys will be conducted among community members to determine their level of awareness of the MDA campaign following mobilization activities in targeted communities (Table 2).

**Table 2 Tab2:** Qualitative sample size and participant eligibility for the ETAS study

Thematic Areas	Aim	Sample size	Eligibility
Pre-MDA FGDs with drug distributors and MDA field supervisors present at the MDA training	Assess the acceptability of the increased number of rounds targeted to children among MDA implementers, and to better understand perceived barrier to access or implementation	3 FGDs with a total of 17 participants	MDA drug distributors and MDA field supervisors who participated in the MDA implementation training
Post-MDA FGDs with participating drug distributors	Assess the feasibility of additional treatment rounds targeted to children amongst MDA implementers	4 FGDs with a total of 24 participants	MDA field supervisors and drug distributors that participated in the extended rounds of MDA
Post-MDA FGDs with participating community members	Assess the acceptability of additional rounds of targeted MDA amongst the community members	8 FGDs with a total of 48 participants	Chiefs, mothers, and guardians/caretakers, regardless of whether their child has participated in the MDA or not
Community awareness survey	To assess the community’s knowledge, and awareness of MDA mobilization activities, and the role of health workers in mobilization for the MDA campaign. To evaluate the impact of communication and messaging to raise awareness of the MDA campaign	6 to 9 communities with a total of 120 to 180 participants	Community members of communities targeted for MDA

*FGD* Focus Group Discussion, *MDA* Mass Drug Administration

Mothers, caretakers, and chiefs from communities receiving enhanced interventions will be recruited for FGDs using purposive sampling. This approach ensures that participants are from different communities and have participated in the relevant activities that will be discussed during their FGD. One FGD will only include chiefs, because they have significant influence within the communities and other participants are unlikely to disagree with them publicly. Drug distributors from the county, recruited for the intervention, will also participate in the FGDs. Each FGD will be conducted for approximately 1.5 h by qualified research assistants who have received a 3-day training on research techniques. One moderator and 1 assistant will be assigned per FGD and will follow a comprehensive interview guide on key themes about the research question. All FGDs with community members and chiefs will be conducted in the local Toposa language. Assistants will audio record the discussions, verbally translate and record the Toposa audio into English, and then transcribe the English audio version. FGDs with MDA field supervisors will be conducted in English. FGD assistants will closely observe participants, their significant interactions, and the dynamics within the group, taking detailed notes on collective themes.

A community survey will be completed following MDA mobilization activities to gauge the community’s knowledge and awareness of the upcoming MDA campaign. The survey will be conducted at 3 time points. The first will be conducted before the first round of MDA in each study arm. Two communities will be randomly selected from each study arm for the survey. The census data from that community (previously collected) will be used to randomly select 20 households to survey. One person from each household will be interviewed for the survey by trained interviewers, with preference given for the female caregiver. The survey will be conducted a second time prior to the child-only treatment rounds in the thrice-treatment study arm, and then the survey will be conducted a third time in the bi-annual study arm prior to the second round of MDA.

### Surveys and trachoma monitoring

Household data collection and trachoma monitoring will take place through population-based surveys at baseline (prior to interventions) and approximately 12 months later. Sample size calculations will assume a TF prevalence of 4% among children ages 1 to 9 years with a precision of 2%, an assumed design effect of 3.0, and a 95% confidence level, for a total sample size of 1,104 children. Adjusting for an assumed non-response rate of 20% yields a population size of 1,325 children targeted for surveying. A multi-level cluster random sampling procedure will be used whereby 30 communities will be selected via simple random sample from a list provided by the South Sudan MOH Trachoma Control Program. We will employ the random sort technique to ensure an equal probability of selection across communities in the sampling frame. An independent sampling statistician will generate random values in SAS 9.4 (SAS Institute Inc.) with the ranuni function and a seed to allow replication of the sample should there be a need to augment the cluster list with additional clusters resulting from shortages in availability due to unforeseen problems in access or eligibility. In the second stage 6 segments of 5 households will be randomly selected through community mapping and segmentation for a total of 30 households in each of the 30 communities. Given an estimated 3.7 people per household, of which 40% are children, we would expect to survey on average 45 children ages 6 months to 9 years present per community. Therefore, for trachoma outcomes, we anticipate examining a total of 1,350 children ages 6 months to 9 years. A new random sample of 30 households from each of the same 30 study communities will be selected for the 12-month impact survey, plus 4 additional communities will be randomly selected from the county for inclusion to monitor trends in trachoma outcomes under standard-of-care, annual MDA, and to inform sample size calculations for a potential future efficacy trial. At each survey, a household questionnaire will collect demographic, socioeconomic, and water, sanitation, and hygiene (WASH) data using standard questions found in trachoma impact surveys [7].

Trained and certified trachoma graders will examine all individuals according to the WHO simplified grading system for trachoma using a 2.5 × magnification loupe and adequate light [30]. Tarsal conjunctivae photographs will be taken of both eyes of each child ages 6 months to 9 years using a cellscope device, a smartphone attachment that illuminates and magnifies the conjunctivae [31]. Photographs will be graded for the signs of trachoma. Conjunctival swabs to detect *Chlamydia trachomatis* (*Ct*) infection will be collected from children ages 6 months to 9 years whereby a gloved grader will firmly draw a swab 3 times over the left conjunctivae, rotating at each pass. Conjunctival swabs will be tested for infection and infectious load using polymerase chain reaction [32]. With the availability of additional funding, a sample of positive conjunctival swabs from each timepoint will be tested for antimicrobial resistance markers within the conjunctival space using genomic sequencing techniques.

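### The survey target of 1,325 children covers only 16.7% non-response, not the stated 20%; the target should be 1,380, and the basis of the household yield needs one clarifying sentence

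*Protocol article*

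**What the plan says.** All the figures are in the Protocol article, section Surveys and trachoma monitoring.

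- **Requirement.** TF prevalence is taken as 4% in children aged 1 to 9 years. The calculation is then made "with a precision of 2%, an assumed design effect of 3.0, and a 95% confidence level". The result is given as 1,104 before any allowance for non-response.
- **Non-response.** "Adjusting for an assumed non-response rate of 20% yields a population size of 1,325 children targeted for surveying".
- **Household yield.** Thirty households are surveyed in each of 30 communities. "Given an estimated 3.7 people per household, of which 40% are children, we would expect to survey on average 45 children" in each community. The sentence goes on to describe these children as aged 6 months to 9 years and present.
- **Total.** "we anticipate examining a total of 1,350 children ages 6 months to 9 years".

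The section Setting, eligibility, and participants ties the 40% share to ages 6 months to 9 years. The Background gives ages 1 to 9 years as the band for the TF elimination threshold.

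**The concern.** The adjustment adds 20% of the required number. Non-response, however, removes 20% of the number targeted, which is the larger figure. Adding 20% therefore cannot restore the requirement, and the stated target is too low under the plan's own assumption.

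This affects how the next figures read. The household yield is just above the stated target, so the plan looks sufficient. It is not above the correct target. Whether that matters depends on two things the text leaves open or mixes:

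- **Absent children.** The text does not say whether the yield is counted before or after absent children are excluded.
- **Age band.** The requirement is set for ages 1 to 9, while the yield is counted from 6 months.

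At stake are the accuracy of a stated sample size and the precision a reader would expect for the TF estimate. The study's main conclusions are not affected.

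**Working it through.** **Inputs, all from the protocol:** p = 0.04, d = 0.02, design effect 3.0, z = 1.96, non-response 20%, 30 communities × 30 households, 3.7 people per household, 40% children.

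**1. Requirement before non-response**

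n = design effect × z² × p(1 − p) / d²

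- 1.96² × 0.04 × 0.96 / 0.02² = 368.79
- 3 × 368.79 = 1,106.4, and 3 × 368 = 1,104

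The stated 1,104 is reproduced when 368.79 is cut to 368 before multiplying. The difference is immaterial.

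**2. Non-response**

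- Plan's figure: 1,104 × 1.2 = 1,324.8, which rounds to 1,325. Reproduced.
- Non-response that this factor covers: 1 − 1/1.2 = 16.7%.
- Examined at 20% non-response: 1,325 × 0.8 = 1,060, which is 44 short of 1,104.
- Correct target: 1,104 / 0.8 = 1,380, which is 55 more than 1,325 (4.2%).

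**3. Household yield, ages 6 months to 9 years**

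- Per community: 30 × 3.7 × 0.40 = 44.4, stated as 45.
- Total: 30 × 44.4 = 1,332. With the rounding, 30 × 45 = 1,350.
- 1,332 and 1,350 both exceed 1,325, and both are below 1,380.

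**4. Two readings of the yield**

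The half-width is 1.96 × √(3 × 0.04 × 0.96 / n). The 1-to-9 share is an assumption: with ages spread evenly from 6 months to the tenth birthday it is 9/9.5.

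| Case | Children examined | Half-width (points) |
|---|---|---|
| Requirement | 1,104 | 2.00 |
| 1,325 targeted, 20% non-response | 1,060 | 2.04 |
| Absentees already excluded, 6 months to 9 years | 1,332 | 1.82 |
| Same, ages 1 to 9 (1,332 × 9/9.5) | 1,262 | 1.87 |
| Absentees not excluded, 6 months to 9 years (1,332 × 0.8) | 1,066 | 2.04 |
| Same, ages 1 to 9 (1,066 × 9/9.5) | 1,010 | 2.09 |

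Starting from 1,350 instead, the third reading down becomes 1,350 and the fifth becomes 1,350 × 0.8 = 1,080 (half-width 2.02).

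**5. Does the assumed age split decide the answer?** No. If absentees are already excluded, the requirement is met as long as at least 1,104 / 1,332 = 83% of the children are aged 1 to 9. If they are not, even the full 1,066 is below 1,104.

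**The case against.** The strongest reply is that only one number is wrong and nothing follows from it. Most of that reply stands.

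- **A reader might infer that 1,350 does not follow from the inputs.** It does. The product 44.4 is rounded up to 45 and multiplied by 30. The inputs are labelled as estimates, and the gap to 1,332 is 18 children (1.3%).
- **A reader might infer that the survey will fall short.** The documents do not support this without a condition. The yield sentence counts children who are present, which may mean that absence is already excluded. On that reading the yield should be compared with 1,104 rather than 1,380, and it is sufficient. The text does not settle the matter.
- **A reader might take the two age bands as a contradiction.** Both are openly labelled. Photographs and swabs cover 6 months to 9 years, so a count for that band has a purpose. What remains is that requirement and yield are not like for like, and the size of the gap rests on an assumed age split.
- **A reader might infer that the plan claims 1,350 covers the requirement, or that future trials would inherit the count.** No sentence makes that claim. The protocol says future trials will draw on the survey's data, not on its planned headcount.
- **The effect is small.** The half-width is 2.09 points at worst, against 2.00. Cost and acceptability are the primary outcomes, and the Discussion says the study was not designed to compare efficacy on trachoma outcomes.

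None of this rescues 1,325 as an adjustment for 20% non-response.

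**Conclusion.** Wrong as written, and minor. The inflation error is certain: it rests only on the plan's 1,104 and 20%. The target is understated by 55 children, and its consequence at the stated non-response rate is a loss of about 0.04 points of precision.

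Whether the household plan delivers 1,104 examined children is unresolved, because the text does not say if the 3.7 people per household and the count of children present already leave out absentees. If they do, the requirement is met with room to spare. If they do not, it is missed by about 38 children (1,104 − 1,066) in the wider band, or about 94 (1,104 − 1,010) for ages 1 to 9 under the even-age assumption. This is a point for clarification, not a demonstrated shortfall.

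**What to change.** In Surveys and trachoma monitoring:

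1. Replace 1,325 with 1,380 (1,104 / 0.8).
2. State whether 3.7 people per household, and the children described as present, already exclude absentees.
3. If they do, compare the yield with 1,104 and note that the requirement is met. If they do not, give about 1,066 children examined and restate the expected precision as about 2.0 to 2.1 points.
4. Beside the figure for 6 months to 9 years, give the expected number examined at ages 1 to 9, with the age distribution used. Under even ages this is about 1,262 or about 1,010, depending on item 2.

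Keep 30 households per community; no extra recruitment is proposed. If absentees are not yet excluded, the plan accepts slightly wider precision and says so. The cost is a few sentences of text. Conduct and the primary outcomes are unaffected.
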